### LABORATORY EVALUATIONS

Any laboratory toxicities that led to a change in treatment, regardless of grade, must be recorded in the CRFs. At baseline, record all laboratory values. For post-baseline assessments, all laboratory values must be documented in the subject's record, but only laboratory values Grade > 2 must be recorded in the CRFs.

All Grade  $\geq$  2 laboratory results must be recorded on the CRFs within 48 hours throughout the course of the study.

Refer to the Division of AIDS Table for Grading Adult Adverse Experiences (see Appendix IV) for toxicity grading.

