#### 6.3.16 Plasma HIV-1 RNA

The screening HIV-1 RNA must have been performed locally within three months of entry. Eligibility will be determined based on the screening value. The pre-entry HIV-1 RNA must be performed within 14 days prior to study entry. The baseline value will be the geometric mean of the pre-entry and entry determination. All tests will be performed locally.

Additional laboratory evaluations (not considered in the Division of AIDS Table for Grading Adult Adverse Experiences):

Red blood cell count (RBC), granulocytes, lymphocytes, monocytes, eosinophils, basophils, prothrombin time, creatinine, amylase, LDH, glucose, total protein, cholesterol and triglycerides, C-reactive protein, direct bilirubin, albumin.

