#### 9.1.3 Dose Escalation Rule

Dose escalation will occur if

- 1) at least 2 subjects were on study until at least 14 days after receiving their study vaccination and
- 2) no subject in the current or lower dose cohort experienced a Primary Safety Endpoint.

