### 9.2 Endpoints

#### 9.2.1 Primary endpoint: Safety

Occurrence of at least one grade 3 or higher adverse event including signs/symptoms, lab toxicities and clinical events that is "possibly, probably," or "definitely" related to study treatment (as judged by the Principal Investigator, including site clinicians on the team) any time from the first day of study treatment until 28 days after LC002 administration.

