#### MISCELLANEOUS

- When two values are used to define the criteria for each parameter, the lowest values will be first.
- Parameters are generally grouped by body system.
- Some protocols may have additional protocol specific grading criteria.

| PARAMETER          | GRADE 1                  | GRADE 2                  | GRADE 3                  | GRADE 4                      |
|---------------------------|---------------------------------|---------------------------------|---------------------------------|-------------------------------------|
|                           | MILD                     | MODERATE                 | SEVERE                   | POTENTIALLY LIFE-THREATENING |
| HEMATOLOGY  |                                 |                                 |                                 |                                     |
| Hemoglobin                | 8.0 g/dL - 9.4 g/dL             | 7.0 g/dL - 7.9 g/dL             | 6.5 g/dL - 6.9 g/dL             | <6.5 g/dL                           |
| Absolute Neutrophil Count | 1000 - 1500/mm      | 750 - 999/mm        | 500 - 749/mm        | <500/mm                 |
| Platelets                 | 75,000 - 99,000/mm  | 50,000 - 74,999/mm  | 20,000 - 49,999/mm  | <20,000/mm              |
| Prothrombin Time (PT)     | >1.0 - 1.25 x ULN               | >1.25 - 1.5 x ULN               | >1.5 - 3.0 x ULN                | >3 x ULN                            |
| PTT                       | >1.0 - 1.66 x ULN               | >1.66 - 2.33 x ULN              | >2.33 - 3.0 x ULN               | >3.0 x ULN                          |
| Methemoglobin             | 5.0 - 10.0%                     | 10.1 - 15.0%                    | 15.1 - 20.0%                    | >20%                                |
| CHEMISTRIES |                                 |                                 |                                 |                                     |
| SODIUM             |                                 |                                 |                                 |                                     |
| Hyponatremia              | 130 - 135 meq/L                 | 123 - 129 meq/L                 | 116 - 122 meq/L                 | <116 meq/L                          |

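### Section 6.3.16 places five laboratory tests outside the toxicity table although Appendix IV grades all five, so a Grade 3 value could go ungraded; separately, the CRF threshold for laboratory values is stated two ways.

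*Protocol*

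**What the plan says.** Section 6.3.16 ends with a list of additional laboratory evaluations described as "not considered in the Division of AIDS Table for Grading Adult Adverse Experiences". The list includes "prothrombin time, creatinine, amylase, LDH, glucose, total protein, cholesterol and triglycerides".

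Appendix IV reproduces the Division of AIDS table. It has graded rows for prothrombin time, creatinine, glucose (low and high), triglycerides and amylase. Section 6.3.10 also lists creatinine in the regular blood chemistries, without any such label.

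The primary endpoint in section 9.2.1 is "Occurrence of at least one grade 3 or higher adverse event including signs/symptoms, lab toxicities and clinical events", judged possibly, probably or definitely related, from the first day of study treatment until 28 days after administration. Section 9.1.3 allows escalation only if "no subject in the current or lower dose cohort experienced a Primary Safety Endpoint".

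Under Laboratory Evaluations in section 6.3, all values are recorded at baseline. After baseline, all values go into the subject's record, but "only laboratory values Grade > 2 must be recorded in the CRFs". The next paragraph says that all Grade ≥ 2 "laboratory results must be recorded on the CRFs within 48 hours throughout the course of the study". A toxicity that changed treatment is recorded at any grade.

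**The concern.** Grade decides three things in this protocol: whether a post-baseline laboratory value normally reaches the CRF, whether it can be a primary endpoint, and whether the next cohort opens. A statement that a test lies outside the grading table is therefore operative text, and for five tests it is wrong.

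With three subjects per cohort, one related Grade 3 event decides escalation. A value left without a grade would remain in the source record unless it changed treatment, and the escalation decision could be taken without it.

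The two CRF thresholds are a separate matter. They cannot both hold, and sites could differ in whether they send Grade 2 results to the database.

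**Working it through.** The protocol gives no figure to reproduce here. The check sets the sections side by side.

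**Step 1: the 6.3.16 list against Appendix IV.** The list has 17 analytes: red cells, granulocytes, lymphocytes, monocytes, eosinophils, basophils, prothrombin time, creatinine, amylase, LDH, glucose, total protein, cholesterol, triglycerides, C-reactive protein, direct bilirubin and albumin. Matching by name gives 5 of 17:

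| Test | Grade 3 band in Appendix IV | Also in a regular panel (6.3.9 to 6.3.11)? |
|---|---|---|
| Prothrombin time | >1.5 to 3.0 x ULN | No |
| Creatinine | >3.0 to 6.0 x ULN | Yes, 6.3.10 |
| Amylase | >2.0 to 5.0 x ULN | No |
| Glucose | 30 to 39 mg/dL (low); 251 to 500 mg/dL (high) | No |
| Triglycerides | 751 to 1200 mg/dL | No |

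Granulocytes and direct bilirubin come close to the neutrophil and bilirubin rows but do not match by name, and are not counted.

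**Step 2: what a literal reading does.** Take a triglyceride value of 800 mg/dL or an amylase of 3 x ULN by Day 28. Both are Grade 3 in Appendix IV. A site that accepts 6.3.16 may assign no grade. Alternatively it may use the estimating scale in Appendix IV, which is meant for abnormalities without a row of their own and grades by limitation of activity and need for intervention. An asymptomatic, untreated amylase of 3 x ULN would then be Grade 1. By either route it misses both CRF thresholds and the endpoint.

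**Step 3: the two CRF thresholds against the endpoint.**

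- Grade > 2 captures {3, 4}.
- Grade ≥ 2 captures {2, 3, 4}.
- The endpoint needs {3, 4}.
- Endpoint grades lost: none under either rule. The rules differ only in {2}.

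**Step 4: illustration of the stakes for escalation.** Let p be the true chance that a subject has a related Grade 3 or higher event, and m the share of such subjects whose event goes unrecorded. Neither is given in the protocol; both are assumed. With three subjects,

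P(no recorded endpoint) = (1 − p(1 − m))³.

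| p | m = 0 | m = 0.10 | m = 0.25 | m = 0.50 |
|---|---|---|---|---|
| 0.1 | 0.729 | 0.754 | 0.791 | 0.857 |
| 0.2 | 0.512 | 0.551 | 0.614 | 0.729 |
| 0.3 | 0.343 | 0.389 | 0.465 | 0.614 |

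For example, p = 0.2 and m = 0.25 give (1 − 0.15)³ = 0.614, against 0.8³ = 0.512 with full ascertainment. The loss can come only from the tests in Step 1, so the larger values of m are upper-range cases and not expectations.

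**The case against.** The strongest defence is that the label in 6.3.16 misdescribes the table but does not instruct anyone to leave a value ungraded. Other text points towards grading. Section 9.2.1 does not limit laboratory toxicities to a list, the laboratory section refers toxicity grading to Appendix IV, and the Signs and Symptoms text in 6.3.6 requires all toxicities on the CRF within 48 hours. This stands as far as it goes: events may be missed, and it is not established that they will be. It does not remove the problem, because 6.3.16 is the specific statement about these tests and a site could reasonably let it govern.

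A reader might also infer more than the documents support:

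- **That the conflicting thresholds let Grade 3 events escape the endpoint.** They do not; both capture Grades 3 and 4.
- **That five tests are dropped from the endpoint.** Nothing is expressly excluded, and creatinine is in the regular panel.
- **That Grade 0 and 1 values are lost.** They stay in the subject's record and are simply not transcribed unless they changed treatment.
- **That the tests are run at every visit up to Week 48.** Neither the schedule in 6.1 nor the list in 6.3.16 gives timing for the additional tests, and Weeks 12 to 48 lie outside the 28-day endpoint window in any case.
- **That selective transcription undermines a planned analysis.** No endpoint in 9.2 is a change from baseline in hematology, chemistry or liver tests.

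**Conclusion.** The point holds in a limited form. Section 6.3.16 contradicts Appendix IV for 5 of its 17 tests and contradicts section 6.3.10 for creatinine. The practical exposure is chiefly prothrombin time, amylase, glucose and triglycerides. The consequence is possible under-ascertainment of the primary safety endpoint, and so of the escalation criterion, where one related event is decisive. It depends on three conditions: the test is measured within 28 days of administration, the site follows the label, and the event would be judged related. Its size cannot be estimated from the protocol.

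The contradiction between Grade > 2 and Grade ≥ 2 is a separate and smaller fault, confined to the completeness of Grade 2 laboratory data. Both should be corrected because grading feeds the only primary endpoint and the correction is nearly free.

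**What to change.** 1. In section 6.3.16, remove prothrombin time, creatinine, amylase, glucose and triglycerides from the list of tests outside the table. State that, whenever measured, they are graded by Appendix IV and count as laboratory toxicities under 9.2.1. Keep creatinine in 6.3.10 only.
2. Under Laboratory Evaluations in section 6.3, state one post-baseline CRF threshold. Grade ≥ 2 agrees with the 48-hour rule there and with the Grade 2 or higher rule for non-local signs and symptoms in 6.3.6.
3. Optionally, record all post-baseline values of the scheduled panels on the CRF. No endpoint in 9.2 requires this, but it would allow laboratory change to be described for every subject.

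Items 1 and 2 cost a text correction and a note to the site, with no new procedure. Item 3 costs modest data entry for 9 subjects at seven scheduled post-baseline visits (Days 7, 14 and 28; Weeks 12, 24, 36 and 48), that is 9 x 7 = 63 subject-visits of values already required in the subject's record.

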### IMMUNOLOGIC STUDIES

#### 6.3.17 CD4/CD8

Obtain absolute CD4/CD8 count and percentages within 14 days prior to study entry from a laboratory. Eligibility for study participation will be determined by the screening measurement, which has to be obtained within three months of entry. A mean of the pre-entry and entry measurements will be used as the baseline value.

Evaluations for CD4+ and CD8+ counts and subset percentage evaluations should be performed at the same laboratory, if possible, for baseline calculation and throughout the course of the study.

Because of the diurnal variation in CD4+ and CD8+ cell counts, determinations for individual subjects should be obtained consistently in either the morning or the afternoon throughout the study, if possible.

NOTE: Each time a CD4/CD8 measurement is obtained, the local laboratory must perform a WBC and differential from a sample obtained at the same time.

Additional cell surface markers (CD45RA, CD45RO) will be evaluated to determine naïve/memory phenotype of CD4 and CD8 T cells.

#### 6.3.18 Virus Specific Immune Response Assays

- a) Quantification of HIV-specific CD3+/CD8+ T cells by flow cytometry using intracellular cytokine (IFN-gamma) staining (1). (VIR Assay, see Appendix III for description).
- b) HIV-specific proliferative responses (LPA, see Appendix III)
- c) Quantification of HIV-peptide pool induced cytokine expressing cells (ELISPOT, ICC, see Appendix III)

NOTE: The immunological assays under b) and c) will be performed by an independent immunological laboratory ([name], Laboratoire d'Immunologie Cellulaire et Tissulaire, Hôpital Pitié-Salpêtrière, Paris, France).

#### 6.3.19 Stored Plasma and PBMC

Plasma and PBMC will be stored according to Appendix III.

#### 6.4 Off-Drug Requirements

Additional 12-week period safety monitoring and reporting of serious adverse experiences (SAEs) continues to be required upon completion or discontinuation of study treatment regardless of whether a protocol follow-up period is scheduled to occur. After 12 weeks OFF study treatment, there are four types of events that must be reported if the relationship to the study drug is assessed by the site physician as definitely, possibly, or unable to judge: DEATHS, NEW ONSET CANCERS, CONGENITAL ANOMALIES, AND PERMANENT DISABILITIES.

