### 6.2.5 Final Study Evaluations

Week 4 will be the final visit in the study treatment phase. Safety follow up continues to 48 weeks after immunization.

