#### 7.1.2 Systemic reactions

Systemic reactions will be graded according to the Division of AIDS Table for Grading Adult Adverse Experiences (see Appendix IV). The Principal Investigator should be contacted within 48 hours for any non-local Grade 3 or 4 reactions (for example, elevated temperatures following immunization) thought definitely, possibly, or probably related to vaccination with LC002.

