### 10.4 Serious Adverse Experience (SAE) Reporting

This protocol follows intensive reporting requirements.

Serious adverse experiences must be reported to the National Institute of Pharmacy and Sponsor's representative in Hungary within 24 hours by telephone. In addition, SAE must be reported to the NIP and sponsor within 3 days by completion of the standard EU SAE reporting form.

|                                    |                                              |
|------------------------------------|----------------------------------------------|
| NIP/OGYI contact:                  | [contact]
[contact]             |
| Sponsor's representative, Hungary: | [contact]
[contact]               |
| Sponsor USA:                       | [contact]
[contact] |

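### Section 6.4 leaves 'probably related' out of the late-event reporting rule, and is not reconciled with Section 10.4 on which SAEs are notified after 12 weeks off treatment

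*Protocol*

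**What the plan says.** Section 6.4 sets two stages. First, "Additional 12-week period safety monitoring and reporting of serious adverse experiences (SAEs) continues to be required upon completion or discontinuation of study treatment". Then, "After 12 weeks OFF study treatment, there are four types of events that must be reported", provided the site physician's assessment of relationship to study drug is one of those listed: "definitely, possibly, or unable to judge: DEATHS, NEW ONSET CANCERS, CONGENITAL ANOMALIES, AND PERMANENT DISABILITIES". The section does not say to whom these events are reported, and it does not say when the 12 weeks begin for a regimen of one application.

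Section 10.4 states the SAE procedure: "Serious adverse experiences must be reported to the National Institute of Pharmacy and Sponsor's representative in Hungary within 24 hours by telephone", followed by a written form within 3 days. It gives no closing date, applies no relatedness condition and does not mention 6.4.

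Two other parts of the protocol grade relatedness differently from 6.4. Section 7.1.2 covers non-local Grade 3 or 4 reactions "thought definitely, possibly, or probably related to vaccination with LC002", and the heading of Section 7.1 has the same three categories. The primary safety endpoint in Section 9.2.1 also counts events that are possibly, probably or definitely related.

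On the length of observation, Section 6.2.5 says "Safety follow up continues to 48 weeks after immunization". The Schema and Section 3.0 instead describe a four-week phase and then a further 48 weeks.

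**The concern.** There are two defects, of different strength.

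The first is the relatedness list. It sits inside a condition that decides whether a late event has to be reported. A list that contains *definitely*, *possibly* and *unable to judge* but skips *probably* takes in the weaker attributions and passes over a stronger one. No reading of the protocol explains that as intended.

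The second is the scope of late reporting. Consider an SAE outside the four named types, such as a hospitalisation at Week 24. Section 10.4 as written calls for notification within 24 hours. Section 6.4 does not name it among the events to be reported by then. The site has no cross-reference telling it which section governs.

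Safety is the only primary objective in Section 1.1, and Section 7.2 treats late risk as real: it plans *nef* genotyping for recombination with the vaccine and follows virologic failures for the full 48 weeks. At stake is prompt notice to the regulator and sponsor of serious events in that period.

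**Working it through.** **Relatedness categories, side by side**

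| Place in protocol | Definitely | Probably | Possibly | Unable to judge |
|---|---|---|---|---|
| 6.4, late events | yes | **no** | yes | yes |
| 7.1 heading and 7.1.2 | yes | yes | yes | no |
| 9.2.1, primary endpoint | yes | yes | yes | no |
| 10.4, SAE reporting | no relatedness condition stated | | | |

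Applied to a new cancer at Week 30: *possibly* related meets the 6.4 condition; *probably* related does not.

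**How much of the follow-up is affected**

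The protocol gives no figure of its own to reproduce. The inputs are:

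- Full SAE reporting after treatment: 12 weeks (6.4).
- Start of off-treatment time, S: Week 0 if it is the single Day 0 application (5.1), or Week 4 if it is the end of the treatment phase at Day 28 (6.0, 6.2.5).
- End of follow-up, E: Week 48 (6.2.5), or 4 + 48 = Week 52 (Schema, 3.0).

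Share of the time from vaccination to the end of follow-up that falls under the four-event list = (E − (S + 12)) / E.

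| S | E | Calculation | Share |
|---|---|---|---|
| 0 | 48 | (48 − 12)/48 = 36/48 | 75% |
| 4 | 48 | (48 − 16)/48 = 32/48 | 67% |
| 0 | 52 | (52 − 12)/52 = 40/52 | 77% |
| 4 | 52 | (52 − 16)/52 = 36/52 | 69% |

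The reduced list begins at Week 12 or Week 16. Of the four follow-up visits in Section 6.1 (Weeks 12, 24, 36, 48), those at Weeks 24, 36 and 48 fall after it on every reading.

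**What is not affected**

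Twelve weeks is 84 days. The primary endpoint window closes 28 days after administration (9.2.1), and the escalation rule looks at 14 days on study (9.1.3). Both close before the reduced list can apply.

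**The case against.** A reader might infer that 10.4 is an unlimited rule which 6.4 flatly contradicts. The text does not go that far. Section 10.4 gives recipients and deadlines and is silent on duration, while 6.4 is the section that speaks to the period. The two can be read as complementary. Section 6.4 also says what must be reported, not that nothing else may be; it reads as a minimum that holds whether or not follow-up is scheduled. A site obeying both sections in full would report every SAE. That stands, and it rules out saying that sites *would* under-report. It does not settle the matter: if 6.4 fixes the period, the duty of expedited notice lapses for most SAE types during scheduled safety follow-up, and if it does not, the protocol never says so.

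A reader might also infer that 6.4 contradicts the 48-week follow-up, or that late events would be lost. Neither is supported. Examinations and laboratory tests continue to Week 48 (6.0, 6.1), and Section 6.3.6 requires signs, symptoms, AIDS-defining events, deaths and toxicities to be entered in the CRF within 48 hours for the whole study. Late events therefore still reach the trial data. CRF entry is, however, not the telephone notice to the regulator and sponsor that 10.4 describes.

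On the missing category, it is fair to say that a site reporting *possibly* related events would probably report *probably* related ones too, and that the omission looks like a slip. Section 7.1.2 gives a partial backstop, with no end date, for non-local Grade 3 or 4 reactions judged probably related, and Appendix IV grades any event deemed serious as Grade 4. That route leads to the Principal Investigator, not to the regulator, so it softens the gap without closing it.

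**Conclusion.** The point holds in this form. The relatedness list in 6.4 is wrong as written: it is an operative safety rule that omits one of the three positive categories used elsewhere in the protocol. That conclusion needs no assumption beyond the literal text.

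The relation between 6.4 and 10.4 is an unresolved ambiguity, not a proven contradiction. It concerns expedited notice of SAEs other than the four named types, and it covers 67% to 77% of the time from vaccination to the end of follow-up. The range depends on two things the protocol leaves open: when off-treatment time starts and whether follow-up ends at Week 48 or Week 52.

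Observation of subjects, CRF data, the primary endpoint and dose escalation are untouched. The protocol should be amended on this point, but the main analysis does not turn on it.

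**What to change.** Three edits:

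1. Add *probably* to the relatedness list in 6.4, so that it covers every positive category in 7.1, 7.1.2 and 9.2.1.
2. Reconcile 6.4 with 10.4 and cross-reference them, so that a single rule states which SAEs go to the regulator and sponsor through the end of scheduled safety follow-up, and name the visit at which that follow-up ends. The documents do not dictate which reporting window to choose; the sponsor must state one.
3. Define when the 12 weeks off study treatment start for a single application: at Day 0 or at the end of the treatment phase.

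The cost is a few sentences, and at most a few additional SAE forms in about nine subjects who are already attending the visits.
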